# High-dose vitamin C on sepsis: Protocol of a prospective, multi-centered, double-blinded, randomized, and placebo-controlled superiority study

**DOI:** 10.3389/fmed.2022.950246

**Published:** 2022-09-15

**Keywords:** high dose, vitaminc, sepsis, antioxidant, clinical trial

## Abstract

**Background:**

Sepsis is an inflammatory syndrome with life-threatening organ dysfunction and high mortality. In the recent 10 years, high-dose intravenous injection of vitamin C, the first-line antioxidant of humans, has received highlighted attention in the field of critical care. The study aims to examine the efficacy and safety of high-dose intravenous injection of vitamin C in the treatment of sepsis.

**Methods and design:**

Here, we are conducting a prospective, multi-centered, double-blinded, randomized, and placebo-controlled superiority study named High-Dose Vitamin C on Sepsis (HDVCOS). A total of 620 participants diagnosed with sepsis in four participating sites across China that satisfy the eligibility criteria will be randomized at a ratio of 1:1 to receive treatment with a high-dose intravenous injection of vitamin C (200 mg/kg/24 h) or placebo (saline) for 4 days. The primary outcome is 28 days of mortality. The secondary outcomes include the incidence of organ failure, Sequential Organ Failure Assessment (SOFA) score change, organ support, the relationship between plasma vitamin C concentration and outcomes, and adverse events.

**Conclusion:**

The findings of this study will provide potential evidence for high-dose intravenous injection of vitamin C in the treatment of sepsis.

**Clinical trial registration:**

[http://www.chictr.org.cn/showprojen.aspx?proj=29851], identifier [ChiCTR1800017633].

## Introduction

Sepsis is defined as an inflammatory syndrome with life-threatening organ dysfunction resulting from a dysregulated host response to infection (1). The global annual incidence of sepsis is up to 31 million cases, including 19.4 million cases of severe sepsis (2). The incidence of sepsis in China is 461 per 100,000 population (3), according to the latest data. The management of sepsis, including antibiotics, source control, fluid resuscitation, vasopressors, and organ support, has improved a lot in the last 30 years, but sepsis-related mortality remains high, with 74 deaths per 100, 000 population worldwide (2) and 66.7 deaths per 100,000 population in China (4). New interventions to improve mortality need to be explored and developed.

After the onset of sepsis, uncontrolled oxidative stress-induced systemic inflammatory response syndrome (SIRS) contributes to progressive organ dysfunction and death (5). In the recent 10 years, a high-dose intravenous injection of vitamin C, the first-line antioxidant of humans, has received highlighted attention in the field of critical care (6). Its beneficial effect in critical illness has been demonstrated by several small-scale clinical trials and animal studies, such as severe burn (7), severe acute pancreatitis (8), ischemic reperfusion injury (9–11), and sepsis (12). Still, the effect of a high-dose intravenous injection of vitamin C on sepsis remains controversial according to the recent retrospective work of the cohort study (13) and the real-world study (14). In the past several randomized control trials, high-dose vitamin C was shown to fail to improve organ function scores and inflammatory biomarkers but to improve the survival rate in sepsis by the results of the CITRIS-ALI study (*N* = 167) (15). However, David et al. failed to demonstrate that intravenous vitamin C therapy could significantly improve the survival rate in patients with sepsis (*N* = 124) (16). Therefore, a larger trial exploring the effect of high-dose intravenous vitamin C on sepsis seems necessary. Therefore, we have designed this prospective, multi-centered, double-blind, randomized, placebo-controlled study to explore the effect of high-dose vitamin C on sepsis.

## Methods and analysis

### Study design

We have designed the High-Dose Vitamin C on Sepsis (HDVCOS) study as a prospective, multi-centered, double-blinded, randomized, placebo-controlled, superior clinical trial. Till now, five centers in China have been involved. The trial protocol is approved by the Clinical Trail Ethics Committee of Ruijin Hospital of Shanghai Jiao Tong University School of Medicine (2018-145) and all the participating centers. This trial has been registered in the Chinese Clinical Trial Registry (ChiCTR1800017633). A total of 620 participants diagnosed with sepsis that satisfy the eligibility criteria will be randomized at a ratio of 1:1 to receive treatment with a high-dose intravenous injection of vitamin C (200 mg/kg/24 h) or placebo (saline) for 4 days.

### Study population

Any patient admitted to the participating sites and diagnosed with sepsis according to sepsis 3 definition (1) will be considered for enrollment. Figure 1 shows the flow chart throughout the study. The recruitment was initiated in August 2019.

**FIGURE 1 F1:**
[figure not shown]
Participants flow chart.

#### Inclusion criteria

The inclusion criteria were as follows:

1.Patients aged above 18 years.2.Patients meeting the diagnostic criteria of sepsis, which is suspected infection and organ dysfunction (total Sequential Organ Failure Assessment (SOFA) score ≥ 2 points).3.Patients within 72 h from the establishment of sepsis diagnosis to inclusion.4.Patients who avoided pregnancy during the whole study period.5.Patients who were able to read and write in Chinese and should provide informed consent.

#### Exclusion criteria

The exclusion criteria were as follows:

1.Patients or their surrogate refuse to receive cardiovascular (vasopressor agent), respiratory (mechanical ventilation), or renal (renal replacement therapy) supports during the treatment period.2.Pregnant patients or in lactation.3.Patients with poorly controlled chronic organ failure, defined as: (1) chronic cardiovascular dysfunction requiring long-term mechanical hemodynamic support or inotropes support, (2) chronic obstructive pulmonary disease requiring home oxygen, (3) chronic hepatic dysfunction classified as Child-Pugh C, (4) chronic renal disease with an eGFR < 60 ml/min/1.73 m^2^ or serum creatinine >150 μmol/L.4.Patients allergic to vitamin C.5.Patients who are participating or have participated in other investigational studies.6.Patients who weigh more than 100 kg.7.Patients with kidney stone.

### Randomization, Blinding, and allocation

Participants are randomly assigned to the vitamin C or normal saline (NS) groups in a 1:1 ratio. The randomization sequence is generated with SAS v. 9.2 (SAS Institute Inc., United States) using stratified block randomization with a block length of 10 and stratified by site. A randomized envelope is made by a statistician in our clinical research center. The sequence number is marked outside the envelope and the medication puzzled for vitamin C or NS is sealed inside. The randomization information is blinded to all the participants in the trials except the unblinding drug preparing nurse (UDPN).

After consent is obtained and the inclusion/exclusion criteria are verified, the principal investigator (PI) in each participating site (PS) hands the unique randomized envelope of the participant to UDPN. The UDPN unseals the envelope and disposes the vitamin C or NS into an opaque 50 ml syringe according to grouping information inside the envelope. UDPN gives the opaque syringe to the therapy nurse and is independent of the following medical process. The outcome assessor and statistician are blinded to randomization and are not involved in treatment procedures.

### Medication and intervention

Patients receive the first dose of vitamin C or NS within 2 h after randomization.

#### Regular treatment

The sepsis 3.0 guideline will be followed for the regular management of patients with sepsis (17). This includes fluid resuscitation, antibiotics, vasopressor titration, mechanical ventilation and ventilator weaning strategies, blood transfusion, nutrition, renal replacement therapy, delirium management, and glycemic control.

Group 1: Vitamin C group

The vitamin C (Brilliant, China) with a dose of 200 mg/kg/24 h is given by continuous injection through the central venous with a speed of 5 ml/h for 4 days.

Group 2: NS group

The.9% NS (Baxter, China) with the same volume as corresponding vitamin C is given by continuous injection through the central venous with a speed of 5 ml/h for 4 days.

### Outcomes

#### Primary outcome

The primary aim of this study is to prospectively assess the effect of high-dose vitamin C therapy on 28 days of mortality in patients with sepsis.

#### Secondary outcomes

The secondary outcomes are as follows:

1.The incidence of organ failure within 28 days: organ failure is defined as at least three points on the SOFA score assigned in a particular organ system (cardiovascular, hepatic, respiratory, renal, and coagulation system) (18).2.Change in the SOFA score on days 1, 3, 7,14, and 28.3.The duration of organ support within 28 days: Organ support is defined as mechanical ventilation, renal replacement therapy, and vasoactive drug application.4.Plasma concentration of vitamin C on days 0, 3, 4, and 7 and its relationship with outcomes and adverse events5.The change of inflammatory indicators (C-reactive protein and procalcitonin) on days 1, 3, 7, 14, and 28.

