### Adverse events

An adverse event (AE) is “any untoward medical occurrence in a human subject, including any abnormal sign (e.g., abnormal physical exam or laboratory finding), symptom, or disease” and occurs during a subject’s participation in research.

AEs include the following:

1.crystal in urine2.respiratory failure3.thromboembolic disease4.arrhythmias5.delirium6.anemia7.coagulopathy

Severe AEs (SAEs) include the following:

1.unexplained acute kidney failure2.life-threatening events3.results in prolongation of the existing hospitalization4.persistent or significant disability/incapacity5.death

Both AEs and SAEs were evaluated at 8:00 am every day. They will be recorded and reported to the PI of each research site and evaluated if they are related to this study. Once confirmed, the given medicine should be discontinued immediately, and the patients should be treated appropriately. Both AEs and SAEs will be reported.

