### Statistical analysis

Categorical data will be described with frequency or ratio. Continuous variables will be described using mean and SD for normally distributed variables or median and interquartile range (IQR) for non-normally distributed variables. Categorical variables will be compared using the chi-square test or the Fisher exact test. Continuous variables will be compared using the t-test for normally distributed variables or the Wilcoxon rank-sum test for non-normally distributed variables. The efficacy analysis will be based on the intention-to-treat principle and compared with the per-protocol principle subset.

The primary outcome of 28 days mortality will be compared between groups using the chi-square test or the Fisher exact test. Superiority could be calculated if the upper bound of 28 days of mortality was lower than the 2.5% superiority margin. Logistic analysis with a 95% CI is used to calculate the odds ratio of each risk factor.

The secondary outcomes of the SOFA score change and inflammatory indicators change on days 1, 3, 7, 14, and day 28 between two groups will be analyzed using a generalized linear model. The incidence of organ failure and adverse events occurrence will be compared using the chi-square tests or the Wilcoxon rank-sum test. The duration of organ support and vitamin C concentration on days 0, 3, 4, and day 7 will be compared using the *t*-test or the Wilcoxon rank-sum test. All these analyses are performed two-sided at the 5% significance level. SAS v. 9.2 (SAS Institute Inc., United States) is used for the analysis.

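### The organ-failure secondary outcome makes no reference to the day-0 SOFA score, so, read literally, failure already present at entry counts as an event and dilutes the comparison

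*Protocol article*

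**What the plan says.** All references are to the protocol article.

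- **Outcome (Secondary outcomes, item 1).** The outcome is named "The incidence of organ failure within 28 days", and "organ failure is defined as at least three points on the SOFA score assigned in a particular organ system". Five systems are listed: cardiovascular, hepatic, respiratory, renal and coagulation. Nothing ties the event to the day-0 score. The text also does not say whether the unit is the patient or the organ system.
- **Entry (Inclusion criteria).** Patients must have "suspected infection and organ dysfunction (total Sequential Organ Failure Assessment (SOFA) score ≥ 2 points", with no ceiling on the total or on any single system. They may be enrolled late in the episode: "Patients within 72 h from the establishment of sepsis diagnosis to inclusion".
- **Exclusions (Exclusion criteria).** The relevant exclusion is "Patients with poorly controlled chronic organ failure". Acute failure caused by the current sepsis is not excluded.
- **Analysis (Statistical analysis).** "The incidence of organ failure and adverse events occurrence will be compared using the chi-square tests or the Wilcoxon rank-sum test". No baseline term and no at-risk set are stated. "All these analyses are performed two-sided at the 5% significance level".
- **Data (Table 1).** The SOFA score is scheduled on day 0 and at every later visit listed.

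**The concern.** Everyone in this trial enters with organ dysfunction, and some will already be at 3 points or more in one system before treatment starts. If the definition is applied as worded, such a patient is an event even if that organ recovers promptly and no other organ fails. A four-day infusion cannot prevent a failure that is already there.

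The comparison would then mix two things: failure present at entry, which randomisation makes equal in expectation, and new failure, which is the only part treatment can prevent. The first raises both rates by a similar amount and narrows the gap between them. A real effect on new failure would look smaller than it is and would be easier to miss. This is the first-listed secondary outcome and the only efficacy outcome that counts whether organ failure occurs.

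**Working it through.** **The plan's own figure.** There is none to reproduce. The article gives no event rate, target effect, power or day-0 prevalence for this outcome. The 620 in the Sample size section is for 28-day mortality and is used here only for the arm size.

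**Inputs from the article.** 620 patients randomised 1:1, so 620 / 2 = 310 per arm; two-sided 5% for secondary outcomes.

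**Inputs that are assumptions.**
- *q*: share of patients with SOFA of at least 3 in some system on day 0, equal in both arms; range 10% to 70%.
- *c* and *t*: new-failure rates under control and vitamin C among patients free of failure on day 0; 30% and 20%, with 40% and 30% as a second case.

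**Step 1: rates under the literal definition.** Control is q + (1 − q)c and vitamin C is q + (1 − q)t. The difference is (1 − q)(c − t), so it falls by exactly the fraction q. The share of control-arm events already present at entry is q / [q + (1 − q)c].

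**Step 2: power.** With p̄ the mean of p1 and p2, SE0 = √[2p̄(1 − p̄)/n] and SE1 = √{[p1(1 − p1) + p2(1 − p2)]/n}, power = Φ[(|p1 − p2| − 1.96·SE0)/SE1]. As written, n = 310 per arm. For new failure among patients at risk, n = 310(1 − q) per arm, with rates c and t.

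**Worked case, q = 30%, 30% versus 20%.**
- As written: 0.30 + 0.70 × 0.30 = 0.51 and 0.30 + 0.70 × 0.20 = 0.44. SE0 = 0.0401, SE1 = 0.0400. Power = Φ[(0.07 − 1.96 × 0.0401)/0.0400] ≈ 41%.
- At risk: n = 310 × 0.70 = 217 per arm. SE0 = 0.0416, SE1 = 0.0413. Power = Φ[(0.10 − 1.96 × 0.0416)/0.0413] ≈ 67%.

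**Results, new failure 30% versus 20%.**

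| q | Rates as written | Difference (points) | Control events present at entry | Power as written | At risk per arm | Power, new failure |
|---|---|---|---|---|---|---|
| 10% | 37% vs 28% | 9 | 27% | 67% | 279 | 78% |
| 30% | 51% vs 44% | 7 | 59% | 41% | 217 | 67% |
| 50% | 65% vs 60% | 5 | 77% | 25% | 155 | 53% |
| 70% | 79% vs 76% | 3 | 89% | 14% | 93 | 35% |

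**Second case, 40% versus 30%.** Power as written versus new failure: 62% vs 70% (q = 10%), 42% vs 59% (30%), 26% vs 45% (50%), 15% vs 30% (70%). The at-risk analysis does better at every q shown, despite having fewer patients.

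**Unit of scoring.** The model takes any failure per patient and treats only patients free of all failure as at risk. Scored per system, a patient with one failed system on day 0 remains at risk in the other four. The day-0 share for one system cannot exceed the share for any system, so the dilution is smaller.

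**The case against.** The best defence is the word incidence, which ordinarily means new occurrence. On that view the SOFA threshold describes a state, and the rule for counting it may be in the full protocol or analysis plan, neither of which is shown. This stands in part: no sentence in the article says that a day-0 failure counts as an event. But the article does define the event, and the definition it gives is met by a patient already at 3 points. Two analysts could follow it and report different results.

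Three further points stand. Randomisation balances day-0 failure in expectation, so the result is dilution and not bias. The outcome is secondary and the sample size was not built on it. The course of failure already present is addressed by SOFA change and by duration of organ support, so organ effects do not rest on item 1 alone.

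Two stronger readings are tempting, and the article does not support them.

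- *That the comparison is swamped.* This depends on the day-0 share, which is not given. A total SOFA of 2 can be reached with no system at 3. At 10% the loss is about 7 to 11 power points; it becomes heavy only from about 30% to 50% upward. The expected 40% mortality makes a high share plausible but does not establish it.
- *That the adverse-event comparison has the same flaw.* Respiratory failure, coagulopathy, anemia and delirium are listed as adverse events, and "Both AEs and SAEs were evaluated at 8:00 am every day", so a reader might infer that conditions present at entry are counted. The Adverse events section, however, confines an adverse event to something that arises while the person is taking part in the research. That is an onset condition, so the point does not extend to adverse events.

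**Conclusion.** The point holds for secondary outcome 1 only. The definition lacks a baseline condition, the entry criteria admit patients who already meet it, and the stated test does not adjust for this. Read literally, the absolute difference shrinks by the share of patients in failure on day 0 and power falls with it. Type I error is not affected and neither arm is favoured.

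The size is conditional. Against an analysis of new failure, the power lost at 30% versus 20% is about 11 points if 10% of patients are in failure at entry, 26 points at 30%, 28 points at 50% and 21 points at 70% (the differences between the two power columns above). These figures rest on assumed event rates, an assumed day-0 share and scoring per patient; per-system scoring reduces the loss. If new onset was intended all along, the defect is one of wording, but the wording still needs to be settled. The primary mortality analysis is not touched.

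**What to change.** Reword secondary outcome 1 as new organ failure: a SOFA component of 3 or more after day 0 in a system that scored below 3 on day 0. Then:

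1. analyse it per system, among patients at risk in that system;
2. analyse it overall as at least one new failure per patient;
3. report failure present on day 0, by system and arm, as a baseline characteristic.

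No new data are needed, because Table 1 already schedules the SOFA score on day 0. The costs are a smaller at-risk denominator in each system and a documented amendment to a trial that has been recruiting since August 2019. The article says that data are analysed at completion, so the amendment can be made, dated and justified before unblinding. The adverse-event definition needs no change on this account.

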### Adverse events

An adverse event (AE) is “any untoward medical occurrence in a human subject, including any abnormal sign (e.g., abnormal physical exam or laboratory finding), symptom, or disease” and occurs during a subject’s participation in research.

AEs include the following:

1.crystal in urine2.respiratory failure3.thromboembolic disease4.arrhythmias5.delirium6.anemia7.coagulopathy

Severe AEs (SAEs) include the following:

1.unexplained acute kidney failure2.life-threatening events3.results in prolongation of the existing hospitalization4.persistent or significant disability/incapacity5.death

Both AEs and SAEs were evaluated at 8:00 am every day. They will be recorded and reported to the PI of each research site and evaluated if they are related to this study. Once confirmed, the given medicine should be discontinued immediately, and the patients should be treated appropriately. Both AEs and SAEs will be reported.

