In this trial, we will give the vitamin C in a way of sustained injection (200 mg/kg/24 h, 1 g/h) for 4 days. Other published studies (12, 15, 22) used the same dosage of vitamin C (200 mg/kg/24 h) for 4 days in total, but they gave vitamin C in a bolus injection way. According to the study by De Grooth et al. (23), a sustained injection of 10-g vitamin C for 48 h led to a sustained level of vitamin C approximately five times above the normal level, which might be more helpful to prevent hypovitaminosis than bolus injection. In our study, we will test the plasma vitamin C concentration with high-performance liquid chromatography on days 0, 3, 4, and 7, and the result may provide information on optimal drug delivery ways and plasma concentrations.

The most concern of high-dose vitamin C safety is its potential harm to renal function and the formation of kidney stones (24). A previous case report showed that high-dose oral intake of vitamin C for 6 years led to high urine oxalate excretion and ureteral stone formation in a 9-year-old child. However, there was no reported case of renal stone as an adverse event of short-term intravenous usage of high-dose vitamin C (25). Furthermore, no adverse event was reported in critical illness clinical trials. Anyway, the renal function change of enrolled patients should receive timely evaluation. Patients with a history of renal oxalate stones will not be enrolled in the study.

There are some limitations to this study. First, the rapid degradation quality of vitamin C and the inconvenient availability of high-performance liquid chromatography could influence the accuracy of plasma vitamin C concentration detection. Second, patients with kidney stones were excluded from the trial, which may exclude most of the patients with sepsis originating from the urinary tract.

Vitamin C is a cheap and easily available agent. We expect that the results of this study will provide a scientific rationale for the use of high-dose vitamin C in improving the prognosis of patients with sepsis.

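### The only kidney-function event named for safety depends on an undefined judgement of cause, so it should not carry the renal safety conclusion

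*Protocol article*

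**What the plan says.** Three parts of the protocol article bear on the point.

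- **Discussion.** It states: "The most concern of high-dose vitamin C safety is its potential harm to renal function and the formation of kidney stones". It adds that "the renal function change of enrolled patients should receive timely evaluation".
- **Adverse events.** An adverse event is defined broadly, as "any untoward medical occurrence in a human subject, including any abnormal sign (e.g., abnormal physical exam or laboratory finding), symptom, or disease". Seven adverse events are then listed. The only renal or urinary one is "crystal in urine"; respiratory failure and coagulopathy also appear, with no condition on cause. The serious-event list opens with "unexplained acute kidney failure" and continues with "life-threatening events", longer hospital stay, lasting disability and death. What makes a kidney failure unexplained is not said.
- **Secondary outcomes, Statistical analysis and Table 1.** Organ failure within 28 days means 3 or more SOFA points in one of five organ systems, the kidney among them. For support duration, "Organ support is defined as mechanical ventilation, renal replacement therapy, and vasoactive drug application". Both are compared between arms, as is the occurrence of adverse events. Urea and creatinine are among the routine laboratory tests. SOFA is scored on days 0, 1, 3, 4, 7, 14 and 28.

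**The concern.** The qualifier asks the clinician to decide why a kidney failed before the event fits the named category. In a blinded randomised trial that decision is unnecessary, because comparing the arms shows whether the drug adds events. It is also hard to make here. Every participant enters with suspected infection and a SOFA score of at least 2, so sepsis can be offered as the explanation for almost any kidney failure. With no definition, one site may use the label freely and another hardly at all.

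The filter also falls unevenly. Sepsis causes respiratory failure and coagulopathy too, but those are listed without regard to cause. The organ of greatest stated concern is the one with a condition attached.

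Efficacy and safety are both stated aims. A low count of unexplained kidney failure, similar in the two arms, could be read as renal reassurance when it partly reflects how the label was applied.

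**Working it through.** **Is there a figure to reproduce?** No. The article gives no kidney-event rate, no share of events called unexplained and no power for safety. Everything below is illustration.

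**Which routes admit a kidney event?**

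| Route | Condition on cause? | Identifies the kidney? |
|---|---|---|
| Named serious event | Yes, undefined | Yes |
| General adverse event definition | No | Only if coded as renal |
| Other serious-event criteria | No | No |
| Organ failure, SOFA 3 or more | No | Only if reported by organ |
| Organ support duration | No | Only if renal replacement is reported separately |
| Change in SOFA score | No | No; the total includes renal points below 3 |

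The one route that both names the kidney and is a safety event is the one with the filter.

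**How much could the filter matter?** Inputs from the article: 620/2 = 310 per arm (dropout ignored) and a two-sided 5% level. Assumed inputs: control rate r = 30%; risk ratio 1.33, giving 39.9% on the drug; share u of background events called unexplained = 10%.

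Power = Φ[(d − 1.96·se0)/se1], where d is the difference in proportions, se0 = √(2·p̄(1−p̄)/310) and se1 = √((p1(1−p1)+p2(1−p2))/310).

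1. *All events counted.* 30% v 39.9%: d = 0.099, se0 = 0.0383, se1 = 0.0381. (0.099 − 0.0751)/0.0381 = 0.63, power 73.5%.
2. *Same share labelled in both arms.* 3.0% v 3.99%, about 310 × 0.03 = 9 control events: d = 0.0099, se0 and se1 both about 0.0147. (0.0099 − 0.0289)/0.0147 = −1.29, power about 10%.
3. *Every drug-caused event keeps the label; only the background is filtered.* 3.0% v 3.0 + 9.9 = 12.9%: d = 0.099, se0 = 0.0217, se1 = 0.0214. (0.099 − 0.0426)/0.0214 = 2.64, power above 99%.
4. *Half of the drug-caused events keep it.* 3.0% v 3.0 + 4.95 = 7.95%: d = 0.0495, se0 = 0.0183, se1 = 0.0182. (0.0495 − 0.0358)/0.0182 = 0.75, power about 77%.

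Over control rates of 20% to 40% at the same risk ratio, power with all events is 49% to 91%. With equal labelling and u from 5% to 20% it is 6% to 20%. If the excess keeps the label, it is 89% to above 99%.

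**Would any-organ failure pick it up?** This applies only if organ failure is analysed as one pooled incidence, which the article does not settle. Suppose a share q of both arms has failure of another organ, independent of the kidney. The any-organ rate is 1 − (1−q)(1−kidney rate).

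- q = 50%: 1 − 0.5×0.70 = 65% v 1 − 0.5×0.601 = 70%; power about 26%.
- q = 70%: 1 − 0.3×0.70 = 79% v 1 − 0.3×0.601 = 82%; power about 15%.

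A pooled measure would dilute a kidney signal without removing it.

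**The case against.** A reader might infer that kidney failure counts for safety only when unexplained, that most kidney events would be discarded, and that the safety comparison is nearly blind to the kidney. The article does not support any of these. Its adverse event definition covers abnormal laboratory findings with no limit on cause, so a creatinine rise qualifies. Both lists are introduced as inclusions and are not said to be exhaustive. Four further serious-event criteria ignore cause. Renal SOFA and renal replacement also ignore cause and are compared by arm, though as efficacy outcomes. No source is given for the proportion of events that would be lost.

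The power illustration can also be challenged. The fall to 10% needs drug-caused events to be filtered as heavily as septic ones; if about half of them keep the label, power is no worse than with all events. And it concerns a single item, so it does not measure the trial's overall ability to see renal harm.

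Finally, a condensed article may leave per-organ tables to the full protocol or the analysis plan. The absence of a kidney-specific comparison from the article is therefore context and not, by itself, a fault.

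All of this stands. What it does not answer is that the article does state an event definition, and the definition carries an undefined condition on cause. The other routes need not identify an event as renal. Staff who see only unexplained kidney failure named may also take explained failure as not reportable, and a later analysis plan cannot recover a site's judgement on an event it never logged.

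**Conclusion.** The point holds in limited form. The only named kidney-function safety event depends on an undefined judgement of cause, in a population where a cause is always at hand, for the harm that the article itself ranks first. The resulting count may differ between sites and can under-count drug-related kidney failure. Other cause-neutral routes remain open, so the trial can still see renal harm, but no comparison stated in the article isolates the kidney.

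The size is unknown. Under the assumed rates it runs from a severe loss (73.5% to about 10%) to no loss at all, depending on whether clinicians who do not know the treatment can tell drug-caused failure from septic failure. That is difficult in these patients, but nothing in the article settles it. The change is worth making because it is cheap and removes the dependence on that judgement.

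**What to change.** For the safety analysis, count every new or worsening acute kidney failure after randomisation, whatever its presumed cause. Define it from creatinine, renal SOFA and start of renal replacement, each relative to day 0. Compare its incidence by arm with a 95% CI, as a named safety outcome. Record the investigator's view of cause in a separate field, and do not rest the renal safety conclusion on the unexplained count.

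Keep this as an analysis outcome only. The Adverse events section links recorded events to a relatedness judgement and, once confirmed, to discontinuation of the study medicine; that pathway stays as written.

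The cost is one extra safety table from data already collected, with more events to tabulate, most of them probably due to sepsis.
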